### Methods and analysis

#### Overall study design

This is a single centre prospective observational pilot study in three groups of 30 participants each: civilians admitted to the Queen Elizabeth Hospital (QEH) in Birmingham with acute moderate-severe TBI, military veterans with diagnosis of a previous TBI and a control group of civilians or veterans with no history of TBI. Patients will undergo visual, biochemical and mental health assessments, as well as patient-reported symptoms and quality of life outcome measures over the course of a 1-year follow-up period (see figure 1 for overview).

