#### Statistical methods

Analyses will include all available data of recruited patients (not restricted to patients with complete follow-up). Between group comparisons will evaluate susceptibility to poor mental health and quality of life outcomes. Longitudinal data may show the latency of onset of mental health and quality of life problems after acute TBI, in order to time future interventions.

Candidate serum and visual biomarkers will be compared between groups and associated with mental health and quality of life outcomes to look for predictive value. Many of these data are continuous and normally distributed and repeated measures data (including data from both right and left eyes). As such, generalised estimating equations will be used to determine changes over time with data from each eye and different time points treated as repeated measures, with a binomial distribution used for binary and ordinal outcomes as appropriate. Trial statisticians in the Birmingham Clinical Trials Team will be engaged for further statistical advice, if required.

This is a pilot study to evaluate longitudinal changes in fluid and visual biomarkers of brain injury, mental health status and self-reported quality of life measures in patients with TBI (civilian and military veterans). As such, sample size is based on:

Statistical advice that in a pilot/feasibility study, 30 subjects in each group are recommended to allow estimation of the parameters of interest.Childs *et al*^36^ who showed a difference of 5 µm in global retinal nerve fibre layer (RNFL) thickness between boxers and controls, an average RNFL thickness of 101 and an SE of 1.8.

Past experience in the concussion clinic suggests that we can follow 80% of patients at the 3-month point (ie, only 20% lost to follow-up). We powered the study to detect a 5 µm change in the RNFL thickness, assuming a correlation of 0.9 between repeated measures (conservative given that in the absence of pathology, RNFL thickness varies very little). Simulated power calculations in R revealed that 24 participants with complete data (recruiting 30 and assuming a 20% drop out) would have >80% power to detect a 2 µm change in RNFL thickness and 100% power to detect a 5 µm decrease.

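### Ordinal outcomes are assigned a binomial distribution, which fits only two-level outcomes; an ordinal model should be named, with small-sample GEE inference as a secondary, conditional recommendation

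*Protocol article*

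**What the plan says.** All the relevant text is in the protocol article under Statistical methods, apart from the group sizes.

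- Model: "generalised estimating equations will be used to determine changes over time with data from each eye and different time points treated as repeated measures".
- Non-continuous outcomes: "with a binomial distribution used for binary and ordinal outcomes as appropriate". No cut-points are given, no other model is named for ordinal outcomes, and the article does not list which outcomes it regards as ordinal.
- Continuous data: "Many of these data are continuous and normally distributed".
- Uses: serum and visual biomarkers are to be compared between groups, and related to mental health and quality-of-life outcomes in a search for predictors.
- Size: a "single centre prospective observational pilot study in three groups of 30 participants each" (Overall study design), with 24 per group expected to have complete data after 20% dropout.
- Trial statisticians "will be engaged for further statistical advice, if required".

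The article does not name a working correlation, a variance estimator or a reference distribution.

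**The concern.** The binomial describes a two-outcome variable, or a count of successes out of a fixed number of independent trials. A response on five ordered levels is neither. An analyst who follows the sentence has two routes. One is to force the ordered score into a binomial likelihood, for instance by rescaling it to lie between 0 and 1. That misstates the variance and treats the levels as equally spaced. The other is to cut the scale in two, which discards information and, with no cut-point fixed, leaves the cut open to choice after the data are seen. The questionnaires in Table 7 (BIVSS, PHQ-9, GAD-7, PCL-5, SBQ-R, AUDIT, EQ-5D-5L) carry the mental health and quality-of-life outcomes, so the sentence could reach a large part of the results.

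The secondary matter is the number of independent units. In GEE these are participants; extra eyes and visits do not add to them. The usual sandwich variance with a normal reference runs small when participants are few, and more so for a participant-level predictor with a long tail. The pilot is meant to inform a larger study, so falsely promising biomarkers could be carried forward.

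**Working it through.** **1. Group size.** 24/(1 − 0.20) = 30, so the article's recruitment and completer figures agree. The checks below use 24 and 30 per group, and 60 and 90 for two and three groups pooled.

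**2. Cost of dichotomising an ordinal outcome.** For a two-group comparison under proportional odds, near the null and at a single visit, information on the log odds ratio is proportional to (1 − Σp_k³)/3, where p_k are the level proportions. For a cut leaving a proportion q on one side, this reduces to q(1 − q).

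*Five equal levels (assumed):*
- Ordinal model: (1 − 5 × 0.2³)/3 = 0.960/3 = 0.320.
- Cut at 40/60: 0.4 × 0.6 = 0.24, and 0.24/0.320 = 75%. In a group of 24 this is worth 0.75 × 24 = 18 participants.
- Cut at 20/80: 0.2 × 0.8 = 0.16, and 0.16/0.320 = 50%, worth 12 participants.

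*Skewed levels (assumed 0.60, 0.25, 0.10, 0.04, 0.01):*
- Ordinal model: Σp_k³ = 0.216 + 0.015625 + 0.001 + 0.000064 + 0.000001 = 0.23269, so (1 − 0.23269)/3 = 0.2558.
- Cut after level 1: 0.6 × 0.4 = 0.24, or 94%.
- Cut after level 2: 0.85 × 0.15 = 0.1275, or 50%.
- Cut after level 4: 0.99 × 0.01 = 0.0099, or 4%.

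The loss is small for a well-placed cut and severe for a badly placed one. The article does not fix the cut.

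**3. Type I error if an uncorrected sandwich z test were used (nominal 5%, two-sided; assumed, since the article states no alpha).**

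*Change within one group.* The closed form is 2·P(t₂₃ > 1.96·√(23/24)) = 2·P(t₂₃ > 1.919) = 6.8% at 24 participants. Simulation with 200,000 runs gives 6.7% at 24 and 6.3% at 30.

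*Difference between two groups.* 6.1% at 24 per group and 5.9% at 30 per group (200,000 runs).

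*Group-by-time term in a full GEE.* With 30 per group, 3 visits, 20% dropout and exchangeable correlation (1,000 runs, Monte Carlo SE about 0.7 points): 6.4% Gaussian, 6.6% binary at 20% prevalence, 6.9% binary at 10% prevalence. With a bias-reduced variance and t reference: 4.0%, 4.9% and 5.6%.

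*Participant-level biomarker as predictor.* With balanced visits and exchangeable correlation, the GEE slope equals the regression of participant means on the biomarker x. The uncorrected variance is Σ(x_i − x̄)²e_i²/S², with S = Σ(x_i − x̄)². The corrected version replaces e_i by e_i/(1 − h_i), with h_i = 1/n + (x_i − x̄)²/S, and refers to t on n − 2 degrees of freedom. With 40,000 runs and no true association:

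| Participants | Normal x: uncorrected | Normal x: corrected | Log-normal x (log SD 1): uncorrected | Log-normal x: corrected |
|---|---|---|---|---|
| 24, one group | 10.3% | 5.2% | 17.8% | 6.4% |
| 30, one group | 9.4% | 5.1% | 16.7% | 6.7% |
| 60, two groups | 7.3% | 4.9% | 13.0% | 6.2% |
| 90, three groups | 6.6% | 4.7% | 11.8% | 6.4% |

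Repeat runs agree to within about half a point. A log-normal biomarker that is logged moves to the normal columns, so logging plus correction brings the error to about 5%.

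**The case against.** **On the ordinal wording.** The clause ends with a qualifier that leaves room for judgement. Dichotomising a scale at a recognised threshold and modelling it as binary is legitimate, if less efficient. A sandwich variance also tolerates a wrong variance function. All this stands, and it limits the point to a correction of wording. It does not remove it: the qualifier names neither an alternative model nor a cut-point, and the sentence as printed pairs ordinal outcomes with a distribution that does not describe them.

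**On small samples.** A reader might infer that P values and intervals will be too optimistic because no correction is mentioned. The article does not support that. It names no variance estimator, and such detail is commonly left to an analysis plan, which is not shown. Its silence is not an error. The 9 to 18% figures also need three things together: one group analysed alone, a participant-level predictor and an uncorrected z test; the upper end further needs an unlogged log-normal biomarker. The article ties GEE explicitly to change over time, where the excess is one to two points. What stands is that a search for predictors is also planned, that the acute group is described as the predictive one, and that a skewed biomarker would stay at about 12 to 13% even with 60 to 90 pooled.

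**On normality.** A reader might take the article to assume that every biomarker is normal. It says only that many of the data are, it gives no biomarker distributions, and GEE does not require normal outcomes.

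**On consequence.** This is a pilot with no confirmatory decision rule described, and the article already states that small groups limit generalisability. That lowers the stakes.

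**Conclusion.** The concern holds in a narrow form. The article assigns a binomial distribution to ordinal outcomes, and for more than two levels this is wrong unless the outcome is dichotomised. If it is dichotomised, a five-level item with equal levels keeps at most 75% of its information, and a skewed one anywhere from about 94% to under 10%. These shares assume proportional odds, a single visit and the level proportions shown; the documents give no level proportions. The loss for a median split of a continuous normal scale is a different quantity and does not measure the loss for five-level items.

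Calling the whole GEE analysis invalid would go too far. Misspecification concerns only ordinal outcomes that are not dichotomised; the continuous and binary models are unaffected.

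The small-sample point is a recommendation, not an error found in the plan. If the uncorrected test were used within one group of 24 to 30, type I error would be about 9 to 10% for a normal biomarker and 17 to 18% for a log-normal one with log SD 1 (an assumption). Within-group change and between-group comparisons would run at about 6 to 7%.

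**What to change.** **Main change.** In Statistical methods, keep the binomial for binary outcomes only. State that outcomes with more than two ordered levels will be analysed with a cumulative-logit (proportional-odds) GEE or mixed model, and say which outcomes are treated as ordinal. Where an outcome is dichotomised on purpose, give the cut-point in advance. The cost is one or two sentences, slightly more analysis work, and reliance on the proportional-odds assumption, which needs checking and may be hard to check where upper levels are sparse.

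**Secondary recommendation, here or in the analysis plan.** For biomarker-outcome associations fitted by GEE within a single group, use a bias-corrected sandwich (Mancl-DeRouen or Kauermann-Carroll) with a t reference on participant-level degrees of freedom, and log-transform biomarkers found to be skewed. The cost is a software option and slightly wider intervals; for a logged biomarker, effects are then read per log unit or per doubling.

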### Study limitations

It is important to point out that there are several limitations of this study. For example, some patients may be unable to commit to all of the study follow-up visits and hence there is a risk that patients might withdraw from the study resulting in potentially low enrolment numbers. Adherence to the follow-up visits is also difficult to ensure and is an inherent problem in all clinical trials and especially in pilot trials of this nature that recruit low numbers. Among the veteran population, there may be different times from their TBI to enrolment in this study and this may confound some of the outcome measures.

### Patient and public involvement

Patients and/or public were not involved in the design of this protocol.

### Ethics and dissemination

#### Research ethics approval

The study involves human participants and ethical approval was approved by the UK Health Research Agency through Northwest Haydock Research Ethics Committee (REC reference of 23/NW/0203).

### Consent

Within both veteran and control groups, participants should have capacity to consent and be willing and able to follow the protocol, except for the acute TBI cohort, who may not have capacity to consent as a result of TBI. Written consent will be obtained by the local research team, which may include the site principal investigator, co-investigators or research assistants. Veterans will be recruited through veteran charities such as Bravo Victor, Blind Veterans UK or other veterans charities and organisations. In the acute TBI groups attending the QEH in Birmingham for head injury, identified participants may not have the capacity to consent and as such, written consultation will be obtained from a personal (ie, relative) or nominated (professional) consultee. However, if a patient regains consciousness and capacity, their consultee will be notified, and the patient will be given the opportunity to provide written consent to remain in the study or withdraw. Unconscious patients will only have blood collected and OCT scans conducted as all other tests require a patient to be conscious and have capacity to complete. The willingness of participants to remain in the study will be re-affirmed at each study visit with the patient or consultee as appropriate. Patients have the right to withdraw from the study at any time, but all data collected will be retained and used in the analysis to avoid bias in assessment of outcomes.

### Data access

The final deidentified dataset will be made fully accessible on reasonable request once the results are published.

### Dissemination policy

The results from this study will be disseminated through our University’s website (http://www.bham.ac.uk) and through open access publication in high impact journals, including both civilian and military publications. We will also present our findings at national and international meetings of learned neuroscience, neuropsychiatry, and military societies.
